#### Moderators

2.4.3

Baseline scores, demographic variables, and BMI will be examined as moderators. Baseline scores, including the number of objective binges and eating disorder severity will be examined given prior research suggests that more severe BED pathology at baseline predicts less improvement in BED pathology at the end of CBT-E treatment (66, 67), and may also predict greater treatment dropout (21). Demographics, such as age, gender, and level of education, will be examined as possible moderators. Lastly, BMI, calculated by dividing the participant’s weight in kilograms by the square of height in meters (kg/m2), will be examined as a moderator.

### Statistics

2.5

#### Sample size and power estimation

2.5.1

The primary objective of the proposed study is to determine whether GSH is noninferior to TAU in efficacy. It is expected that both groups will have a reduction in the number of binge-eating days, and GSH is expected to be noninferior compared to TAU in the reduction of binge-eating days in the previous 28 days at the end of treatment.

To calculate the sample size for this noninferiority trial, the significance level was set at *α* = 0.05, power was aimed at 80%, and the noninferiority margin (*Δ*) was set to 1 (*SD* = 2.4) binge-eating day (68) in the previous 28 days between groups. With these assumptions, *n* = 144 (*n* = 72 per arm) participants will be needed to determine noninferiority. The noninferiority margin and standard deviation are based on noninferiority margins from prior studies examining online treatments to reduce eating disorder behaviors (68, 69) and clinical experts on BED treatment outcomes. Efficacy studies of CBT-E (70) and internet-based guided self-help for BED (68) report a 20% dropout; therefore, 20% more participants will be included to compensate for dropout. The sample size corrected for dropout is *N* = 180 (*n* = 90 per arm); therefore 180 participants will be randomized. This sample size calculation was performed using the R package ‘SampleSize4ClinicalTrials’ (71–73) based on a continuous outcome, noninferiority design.

#### Randomization

2.5.2

Randomization will be performed using a 4, 6, 8 block design by Castor Electronic Data Capture (Amsterdam, the Netherlands, 2019) and will take place after the baseline assessment. The allocation ratio will be 1:1. This software will ensure the concealment of allocation and blinding. Stratification will take place based on a BMI of 19.5 ≤ 35 or 35.1 ≤ 40.

#### Statistical analyses

2.5.3

To measure the efficacy of treatment on the reduction of binge-eating days, the number of binge-eating days will be reported as means (standard deviation) between groups and analyzed using a general linear mixed model. Effect sizes will be calculated using Cohen’s *d* (0.2 small, 0.5 medium, 0.8 large; 74) and adjusted for bias (75). Sensitivity analyses will be conducted to test the robustness of the results; given the 20% anticipated dropout rate, analyses will be run on an intention-to-treat protocol, and multiple imputations will be used to handle missing data. To examine possible treatment moderators, a regression analysis with subgroups will be performed by analyzing interaction terms between the moderators and treatment group. Data will be nested within BMI groups (19.5 ≤ 35 and 35.1 ≤ 40) and include random and fixed effects. If significant interactions exist, *post-hoc* analyses will be performed to further explore the moderation.

The cost-effectiveness and cost-utility analyses will be performed from a healthcare perspective. The cost-effectiveness analysis will examine the reduction in binge-eating days as the measure of effect measure, and the cost-utility analysis will use QALYs as effect measure. Differences in costs and effects between groups will be calculated as the difference in cumulative direct costs using the reduction of binge-eating days as the outcome measure. ICERs will be calculated as ICER = (Costs GSH − Costs TAU)/(Effects GSH – Effects TAU) with reduction in binge-eating days as the effect. ICERs to report comparative differences in QALYs will be calculated as ICER = (Costs GSH − Costs TAU)/(Effects GSH – Effects TAU). The costs, effects, and ICERs will be plotted on a cost-effectiveness plane to demonstrate the differences between the costs and effects of both groups, with TAU positioned at the origin of the cost-effectiveness plane. Cost-effectiveness acceptability curves will be used to examine the probability that the cost-effectiveness of GSH is equally as effective with lower costs compared to TAU by a willingness-to-pay for each unit of effect (reduction in binge-eating days or QALYs). The willingness-to-pay for each additional unit of effect in the Netherlands ranges between €20,000 and €80,000 per QALY (25, 76) and €22–€110 per binge-free day in the United Kingdom and the United States (31). All statistical analyses will be conducted using R (77) and SPSS (78).

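### The moderator analysis nests data within two BMI groups with random effects; a two-level variance cannot be estimated reliably, so the BMI randomization stratum should enter as a fixed effect

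*Protocol article*

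**What the plan says.** Section 2.5.3 (Statistical analyses) of the protocol article first says that binge-eating days will be "analyzed using a general linear mixed model". It then turns to moderators: "a regression analysis with subgroups will be performed by analyzing interaction terms between the moderators and treatment group". The next sentence is the one at issue: "Data will be nested within BMI groups (19.5 ≤ 35 and 35.1 ≤ 40) and include random and fixed effects". Post-hoc exploration of significant interactions follows. The section does not say which terms are random, or whether the nesting also applies to the primary mixed model.

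Section 2.5.2 (Randomization) uses the same two bands: "Stratification will take place based on a BMI of 19.5 ≤ 35 or 35.1 ≤ 40". Section 2.2.1 (Eligibility criteria) limits BMI to 19.5 to 40 kg/m², so the bands together span the eligible range. Section 2.4.3 (Moderators) gives BMI a further role: "Lastly, BMI, calculated by dividing the participant’s weight in kilograms by the square of height in meters (kg/m2), will be examined as a moderator". The article nowhere says that the BMI stratum enters a model as a fixed covariate.

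**The concern.** A random effect suits a grouping factor whose levels can be treated as a sample from a larger population, such as therapists or centres. The two BMI bands are not that. They were chosen by the investigators, there are no others, and they are already the randomization strata. Treated as random, they require a between-group variance to be estimated from two values.

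BMI also has two roles that are not reconciled. It is a level of nesting in section 2.5.3 and a moderator in section 2.4.3. If BMI group were entered as a fixed factor in a model that also has a random intercept for BMI group, the random variance would not be identified, because the fixed term already explains all the difference between the two groups.

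At stake are a moderator model that may fit on the boundary or fail to converge, and a stratification factor whose adjustment would depend on a variance estimate that carries almost no information.

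**Working it through.** **1. The plan's own sample size.** Inputs from section 2.5.1: "the significance level was set at *α* = 0.05, power was aimed at 80"%, and a margin that "was set to 1 (*SD* = 2.4) binge-eating day (68"). The true difference is taken as 0.
- n per arm = 2 × (z₁₋α + z₀.₈₀)² × SD² / margin²
- One-sided 0.05: 2 × (1.645 + 0.842)² × 5.76 / 1 = 71.2, so 72 per arm and 144 in total. With 20% dropout, 144 / 0.8 = 180. Both stated figures reproduce.
- One-sided 0.025: 90.4, so 91 per arm and 182 in total. This does not match, so the plan's figure corresponds to one-sided 0.05.

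**2. Information on a variance from k groups.** With group means known without error, the variance estimate has k − 1 df.
- Relative SE = √(2/(k − 1)): 141% for k = 2, against 71% for k = 5 and 47% for k = 10.
- For k = 2 the 95% interval runs from 1/χ²₁(0.975) = 0.20 to 1/χ²₁(0.025) = 1018 times the estimate. On the SD scale that is 0.45 to 32 times.

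**3. How often the variance fits as zero.** With N = 144, residual SD 2.4, stratum sizes n₁ and n₂, and d the difference between stratum means, the truncated estimate is max{0, [d² − s²(1/n₁ + 1/n₂)]/2}. The article gives neither the stratum shares nor the between-stratum SD, so both are assumed. Each cell is 100,000 simulated trials.

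| Share in upper BMI stratum | True SD 0 | True SD 0.5 day | True SD 1 day |
|---|---|---|---|
| 20% | 68% zero | 44% zero | 26% zero |
| 35% | 68% zero | 39% zero | 22% zero |
| 50% | 68% zero | 38% zero | 21% zero |

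When the true variance is 1, the central 95% of estimates runs from 0 to about 5.3–5.6.

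**4. Random intercept only: the treatment contrast.** In 200 simulated data sets (N = 144, 50 in one stratum, arms balanced within strata, a 0.5-day difference between strata), a random intercept for BMI group and a fixed stratum effect gave the same treatment estimate. The SEs averaged about 0.40 and differed by at most 0.0015. The variance fitted as essentially zero in 40% of the data sets.

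**5. Random intercept only: the BMI-by-treatment test.** Here BMI was assumed uniform over 19.5 to 40, with a true interaction of 0 or 0.1 day per BMI unit and 150 data sets each. The interaction SE with random intercept versus fixed stratum was 0.0675 versus 0.0676 (true 0) and 0.0679 versus 0.0680 (true 0.1). Rejection rates were 2.7% versus 2.7% and 36% versus 35%. Many random-intercept fits gave convergence or boundary warnings, and 7 of 300 were unusable. A repeat with other random numbers gave the same picture.

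**6. If treatment were also random by BMI group (not stated in the article).** The SE of the treatment contrast is 2.4 × √(2/72) = 0.40 day. With small-sample inference on 1 df:
- One-sided 0.05: 6.31 × 0.40 = 2.5 days, against 1.645 × 0.40 = 0.66 day.
- Two-sided 0.05: 12.71 × 0.40 = 5.1 days, against 1.96 × 0.40 = 0.78 day.

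Both 1-df half-widths exceed the 1-day margin, before any between-group variance is added.

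**The case against.** The strongest reply is about scope and consequence. The sentence stands inside the moderator analysis, between the interaction regression and its post-hoc step, and nothing carries the nesting back to the primary mixed model. The article does not name the random terms, so BMI group as the random factor is an inference, although it is the only grouping level named. Steps 4 and 5 show that an intercept-only model does little harm to either the treatment contrast or the moderation test. All of this stands, and it limits the point.

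A reader might infer several stronger things that the article does not support:
- **Noninferiority becomes unattainable.** This needs a random treatment effect by BMI group, a small-sample df method, and application to the primary model. The article states none of these.
- **The variance cannot be estimated at all.** It can be computed with 1 df; it is merely uninformative. It is unidentified only if BMI group is also a fixed factor in the same model.
- **The nesting absorbs the BMI moderation effect.** A random intercept can take up part of the BMI main effect. It does not take up the BMI-by-treatment interaction, which is what the moderator analysis tests.
- **The plan wrongly lacks a patient-level random effect.** The article does not exclude one, and the full list of terms may properly be left to the full protocol or SAP.

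What the reply does not answer is that the nesting is a stated choice and not an omitted detail, and that making two exhaustive strata a random factor gains nothing over a fixed effect.

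**Conclusion.** The point holds as a weakness of specification in the moderator analysis. On its natural reading, section 2.5.3 makes the two randomization strata a two-level random factor. Its variance has 1 df and will often fit as zero or bring boundary or convergence problems. It also sits unreconciled with BMI as a moderator.

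The effect on results is small if only an intercept is random, and the sample size is unaffected. It would be large only under a random treatment effect by BMI group, which the text leaves open but does not state.

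The 1-df argument needs no figures from the trial. The zero-fit rates rest on assumed stratum shares (20% to 50%) and between-stratum SDs (0 to 1 day), and the interaction comparison on an assumed uniform BMI distribution.

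**What to change.** Replace the sentence on nesting in section 2.5.3 with: 'BMI stratum (the randomization stratum) is included as a fixed effect, not as a random or nesting factor, and moderation by BMI is tested by a fixed BMI-by-treatment interaction.' Use the same fixed stratum term in the primary mixed model, so that the analysis follows the groups the trial randomizes by.

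The cost is one degree of freedom and a change of wording. No between-group variance has to be estimated, no further data are needed, and N stays at 144 evaluable and 180 randomized.

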#### Data monitoring

2.5.4

All data will be stored in the secure data storage environment within the primary institute and will only be accessible to relevant senior researchers and the project leader with secure login procedures. All data will be handled confidentially, and each participant will be provided with an identification code to separate their personal information from their data, in line with the EU General Data Protection Regulation (79) and the Dutch Act on Implementation of the General Data Protection Regulation (Uitvoeringswet *AVG, UAVG).* Data will be monitored by a statistician and data steward independent from the study, who will review the data collected to ensure the validity of the study findings. Any significant harmful events or reactions possibly relating to the intervention will lead to unblinding. The study will be temporarily halted if there is sufficient ground to suggest that continuing the study could jeopardize the health or safety of a participant. Any participant exhibiting a psychiatric crisis will be assessed and treated accordingly, and any serious adverse events will be reported to the METC. Finally, posttrial support will be offered to participants who require it.

## Anticipated results

3

It is expected that at the end of treatment, the difference in reduction of binge-eating days between web-based GSH CBT-E and TAU CBT-E is within the noninferiority margin (Δ) of 1 binge-eating day (68). Regarding secondary outcomes, it is expected that there will be no difference in the rate of full remission, clinical impairment, or reduction in body shape dissatisfaction between groups. However, it is expected that more severe binge-eating pathology at the start of treatment will predict a weaker treatment response, regardless of condition (80). In addition, the economic evaluation is expected to demonstrate that GSH is more cost-effective than TAU, while having similar cost-utility (31, 81). Therapeutic alliance is expected to be the similar between groups (82). Attrition rate is expected to be approximately 20% in both conditions (68, 83). As for moderators, it is expected that baseline scores will moderate the treatment effect; for example, it is expected that participants with a greater number of objective binges at baseline will demonstrate a slower response to treatment (84). Demographic information is expected to have no effect on the reduction of binge-eating days. Lastly, is expected that BMI will have a small moderating effect on binge-eating reduction, such that participants with a greater baseline BMI will have a weaker response to treatment, regardless of group.

## Discussion

4

This protocol outlines a randomized controlled trial comparing clinical and economic outcomes between two web-based treatments for BED: web-based GSH CBT-E and TAU CBT-E. This study will be the first to directly compare the efficacy of a low-intensity and low-cost alternative compared to TAU CBT-E alongside a complete economic evaluation. Furthermore, this study will establish whether the improvements seen in 20 weeks of TAU CBT-E can be achieved in 12 weeks of web-based GSH CBT-E. The aim of the proposed study is to determine whether web-based GSH CBT-E is noninferior to TAU CBT-E in reducing the number of binge-eating days at the end of treatment. Additional outcomes including full remission, body shape dissatisfaction, therapeutic alliance, clinical impairment, health-related quality of life, attrition, and an economic evaluation to assess the cost-effectiveness and cost-utility of web-based GSH CBT-E and TAU CBT-E will be evaluated to provide a thorough understanding of the efficacy and effectiveness of web-based GSH CBT-E and for whom it is best indicated. Baseline scores, demographic variables, and BMI will be examined as moderators to support the development of a personalized approach to treatment and to optimize the allocation of treatment resources.

The findings from this study will offer compelling insight into whether BED can be treated using a stepped-care model, whereby web-based GSH CBT-E is offered as the recommended first line of treatment for patients in the Netherlands. In this model, if a patient does not improve after web-based GSH CBT-E, they will be offered the higher intensity video conferencing CBT-E. If web-based GSH CBT-E is noninferior to TAU CBT-E in reducing the number of binge-eating days, the treatment can be widely disseminated among allied healthcare workers who identify a patient with BED. This will allow more patients to receive timely support and shorten treatment waitlists, ultimately supporting more patients in their BED recovery.

## Ethics statement

The study has been approved by the Medical Research Ethics Committees United on May 25th, 2021, case number NL76368.100.21. The participants will provide their written informed consent to participate.
